### Need for a Trial (Innovation Aspect)

RP is the commonest of inherited retinal disorders, with a great economic impact and poor associated quality of life [68]. In addition, there is a lack of standard treatment with a good level of efficacy data, which brings a fruitful opportunity to add new knowledge and pursue evidence-based interventions.

The innovation in this study is based on a noninvasive approach—SWL-blocking filters combined with OM. This treatment protocol might represent a better option for patients with RP, especially those with moderate or severe RP, who present with greater functional disability, glare symptoms, and variations in cortisol, salivary α-amylase (sAA), and melatonin levels.

Although a few trials have assessed the efficacy of different vitamins and melatonin in visual and sleep pattern anomalies in patients diagnosed with RP, none of them used a similar combined therapy and even fewer focused on variations in cortisol, sAA, and melatonin levels or determined the impact of these interventions on psychological factors. This study aims to fill this gap in the literature by enhancing the level of evidence with a double-blind RCT that evaluates the benefits that OM combined with SWL-blocking filters may bring to patients with moderate or severe RP.

### Significance/Impact of the Study

RP is accompanied by significant disability, greater dependency, and a decrease in the health-related quality of life, with increased rates of admission to institutional facilities [68-70]. It is also considered a public health issue and a primary cause of headaches, sleep disturbances, and increased rates of depression [71]. Patients with RP also face difficulties in performing daily activities and increased risk of cardiovascular, metabolic, and psychiatric disorders [68-70]. Productivity losses for patients with visual impairment are likely to be amplified in patients with RP because of the early age at onset, vision challenges at school, and loss of visual function without some type of rehabilitation during prime working years [68-70].

The annual cost of adult vision problems for the National Health Service (NHS) is around US $51.4 billion. Among adults with retinal diseases, the annual total health care costs were estimated to be US $7317 higher per patient with RP, increasing the community costs by around 2.5 times because of the number of years of blindness experienced [72].

SWL-blocking filters and OM have been playing an important role in the treatment of several kinds of retinal conditions and sleep disabilities [42,43,47,60,61,73]. Unlike other expensive treatments for sleep disorders, anxiety, and depression, SWL-blocking filters or OM may provide effective control of the human circadian clock through changes in the HPA axis or the retinal–SCN–pineal axis, which could be positively correlated with improvement in the quality of life and visual function disability.

Some studies suggest a multidisciplinary treatment program that includes specialists from different areas of expertise [74]. This program provides a combination of drug treatment and SWL-blocking filters with an adequate assessment of the grade of severity (via clinical assessment) and biochemical stress (by analyzing biomarkers) and determines the impact of psychological factors on patients with RP. It could be considered a good alternative for patients with moderate and severe RP who have not benefited from expensive therapies (eg, bionic eye or genetic therapy) individually. Therefore, in this study, we suggest mimicking a multidisciplinary treatment by combining treatments and analyzing the impact of biochemical and psychological factors on anxiety and sleep disability.

### Choice of Comparators

To date, therapeutic approaches for RP are restricted to slowing down the degenerative process; treating ocular complications, such as cataracts and macular edema; and helping patients cope with the social and psychological impacts of blindness. In addition, the evidence from RCTs on the visual protective effects of vitamins and nutritional supplementations in patients with RP is limited and in some cases contradictory. Moreover, as mentioned before, few studies on the effects of blocking SWL on visual discrimination capacity in patients with RP have been reported. In addition, in clinical practice, there is insufficient experience to recommend the use of optical absorbing filters, since their potential effects on regulating the human internal circadian (24-hour) clock in patients with RP are yet unknown.

For this reason, the intervention groups will consist of SWL blocking alone (SWL group), OM therapy alone (OM group), and SWL blocking plus OM therapy (SWL+OM group) in order to determine whether there is any summative effect. No intervention has been chosen for comparison to avoid performance bias and other biases related to loss of blinding in the trial. Therefore, as several treatments have been proposed to slow down the degenerative process and the current evidence from their results is still limited, no intervention as the control group is justified for this study.

## Methods

### Overview

This parallel-group RCT will be performed at a single institution, which is a tertiary referral hospital with an affiliated research institute (Institute of Applied Ophthalmobiology [IOBA], University of Valladolid). The retinal units in both institutions are highly specialized to manage inherited retinal dystrophies and other related retinal eye diseases. Additionally, the IOBA has a clinical trial unit that could help with the local ethical requirements for running a clinical trial and any oversight or external auditing of data that is needed.

There will be 4 parallel groups of patients. Recruitment will be facilitated by a local foundation for patients with retinitis pigmentosa called the Retina Castilla y León (ReCYL) and will be tightly supervised by an ophthalmologist with specialization in retinal degenerations. Figure 1 provides a summary of the clinical pathways.

A draft intervention protocol will be developed for each group, covering preintervention, intervention, postintervention, and discharge settings based on the literature. A steering committee comprising ophthalmologists, opticians, nurses, psychologists, and the research team will be created to develop these protocols. Additionally, 2 ophthalmology residents will be included. Finally, 1 patient with RP, who is the current president of the Federation of Inherited Retinal Dystrophies’ Associations, will be included in the steering committee. The steering committee members are experts in their respective fields and have used the existing literature (summarized in the *Background and Rationale* section) to inform the inclusion of the different interventions in the protocols. The draft intervention protocols are presented in Table 1. Although the choice of each intervention in these protocols will be informed by the literature [7,28,30,36,51,57,67,75-82] and expert consensus of the steering committee, the study will assess the efficacy of combined interventions in sleep disorders and stress control in a large group of patients with RP. Before the intervention period, all patients will be asked to complete sleep diaries for 2 weeks. In addition, patients in the intervention groups (SWL, OM, SWL+OM) must complete them during the intervention period (30 days). Patients from the SWL and SWL+OM groups will wear SWL-restricting goggles in bright-light conditions and when using light-emitting diode (LED) electronic devices for the 30 days of intervention. Patients from the OM and SWL+OM groups will take 3 pills of Circadin 2 mg (OM) every evening at 10:00 P.M. with a margin of 30 minutes before and after.

A preintervention time of 1.5 years will be necessary for recruitment, informed consent, eligibility screening, and baseline data collection. Next, patients will be randomized to 4 groups in a 1:1 ratio. The treatment groups will include SWL with or without the use of OM. The control group will include patients who are eligible for the study but not willing to be randomized to an intervention sleep and stress management pathway. When the intervention phase (4 weeks) is over, all patients will be followed up for 6 months via standard monitoring. Figure 2 provides a summary of the RCT timeline.

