### Study Population

The study population will comprise patients aged 18-65 years with a history of moderate or severe RP with a grading severity scale score of >1 point according to Iftikhar et al’s [83] scoring criteria. Eligible patients who provide written informed consent will be randomized to 1 of the 4 study groups. Outcomes will be assessed at multiple time points: at baseline in the preintervention period; then at 1, 2, 3, and 4 weeks of the intervention period; and then at 6 months postintervention.

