### Patient Selection, Recruitment, Randomization, and Blinding

#### Eligibility

Eligibility will be determined based on the inclusion and exclusion criteria listed in Table 2. Eligible participants will be identified after initial evaluation by a staff ophthalmologist, determined to satisfy 1 of the qualifying procedures, and approached for informed consent by the ophthalmologist and research staff. At this time, patients will watch an introductory video explaining the purpose of the clinical trial. The physician also will lead an in-depth preintervention discussion explaining each approach to stress and sleep disability (SWL and OM vs control) and postintervention expectations. If patients decline to participate in the RCT, they will be presented with the option of enrolling in the control group (no intervention). There will be no restrictions on patient care due to enrollment in the study.

**Table 2 table2:** Inclusion and exclusion criteria at screening.

Inclusion criteria	Exclusion criteria
Age 18-65 years, from ReCYL^a^ Diagnosis of moderate or severe RP^b^ (grading severity scale score>1 point) Visual function enough to tolerate and see through the optic filters during daily activities Written informed consent provided	Underwent any ocular surgery within the previous 6 months Involvement in any other ongoing clinical trial Pregnancy and lactation or under hormonal treatment Allergy or hypersensitivity to melatonin Previous or current therapy with melatonin Autoimmune diseases NSAID^c^ and others anti-inflammatory drug treatment Psychiatric disorders or under any psychotropic medication

^a^ReCYL: Retina Castilla y León.

^b^RP: retinitis pigmentosa.

^c^NSAID: nonsteroidal anti-inflammatory drug.

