#### Randomization

All patients who provide written informed consent for participation and meet the eligibility criteria will be randomized and assigned using the online SAS Proc Plan permuted-block randomization with variable block sizes and assignments in sequentially numbered codes provided by the central randomization service on its website [94]. The randomization code will not be released until the patient has been recruited into the trial after baseline measurements have been completed.

An administrative assistant not otherwise involved in the study will provide the next treatment code in the sequence and will record the assignment in a confidential log.

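### The protocol says the control arm is randomised but also admits patients who decline randomisation, so comparisons with the pooled control lose the protection of randomisation

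*Protocol article*

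**What the plan says.** Two statements put the control arm inside the randomisation:

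- Methods, Overview: "Next, patients will be randomized to 4 groups in a 1:1 ratio".
- Study Population: "Eligible patients who provide written informed consent will be randomized to 1 of the 4 study groups".

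The Randomization section is consistent with these ("All patients who provide written informed consent for participation and meet the eligibility criteria will be randomized"), but it mentions neither the number of groups nor the control arm.

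Two statements take the control arm, or part of it, outside the randomisation:

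- Methods, Overview, two sentences after the 1:1 statement: "The control group will include patients who are eligible for the study but not willing to be randomized". The rest of that sentence specifies that the refusal concerns an intervention programme.
- Eligibility: "If patients decline to participate in the RCT, they will be presented with the option of enrolling in the control group".

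The Statistics section compares the intervention arms with the control in a linear mixed model of cortisol, melatonin and salivary amylase. The Conclusion frames a positive result as the combination being superior to no intervention. Nothing in the article says that decliners would be analysed apart from randomised controls.

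**The concern.** A patient who declines the trial and then joins the control group has chosen no treatment. That choice may be related to how badly the patient sleeps and to stress-related factors. Sleep quality by the ESS and PSQI is a primary outcome, alongside salivary amylase, cortisol and melatonin (Primary Outcome Measures). If decliners would have changed differently from randomised patients without any treatment, the difference appears in the analysis as a treatment effect, or hides one.

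All three active arms share this control, so the same bias enters all three contrasts with it. A larger sample does not remove it. The intention-to-treat rule in Missing Data gives no help, because a patient who was never randomised has no randomised assignment to be analysed under.

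**Working it through.** **1. Can the passages be reconciled?** Under the first pair of statements, every control patient has been randomised. Under the second pair, some or all have not. The verb used in Overview (include) allows a control arm made up wholly of decliners or a mixture. Only a control restricted to randomised patients would keep the comparison randomised, and the article states no such restriction.

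**2. The plan's own sample size.** Sample Size Calculation gives 12 per group, alpha 5%, Cohen d 1.2 and power 80.02%, then 15 per group after about 20% for dropout. For a two-sample t test (two-sided, an assumption because the sides are not stated):

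- noncentrality = d × √(n/2) = 1.2 × √6 = 2.94, df = 22, power 80.2%. This agrees with the stated figure.
- 12 / (1 − 0.20) = 15 per group, 60 in total. This also agrees.

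The calculation assumes that groups are exchangeable apart from treatment. A self-selected control does not guarantee that. (The same section also mentions an effect size of 0.6, which is a separate matter.)

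**3. What self-selection could do.** Assumptions, none of them in the documents:

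- There is no treatment effect.
- Decliners' mean change differs from that of randomised patients by b SD.
- A share p of the controls are decliners.
- The test is an unadjusted two-sided t test at 5%.

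The group means then differ by p × b, and the noncentrality is p × b × √(n/2). For example, p = 1, b = 0.5 and n = 12 give 0.5 × √6 = 1.22. With p = 0.5 it is 0.25 × √6 = 0.61.

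False-positive rate per contrast with control (nominal 5%):

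| Decliner difference b | Share of decliners p | n = 12 per group | n = 15 per group |
|---|---|---|---|
| 0.3 SD | all | 10.8% | 12.5% |
| 0.3 SD | half | 6.4% | 6.8% |
| 0.5 SD | all | 21.6% | 26.2% |
| 0.5 SD | half | 9.0% | 10.1% |

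The rows for half treat the SD as unchanged. Mixing adds p(1 − p)b² to the control variance, at most 0.5 × 0.5 × 0.5² = 0.0625 here, which is small. The rate rises with n because the bias stays fixed while the standard error shrinks.

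**4. Which contrasts are affected?** Those that use the control: filters, melatonin and the combination, each against no intervention. Comparisons among the three active arms involve only randomised patients and keep their validity. They include the combination against each single intervention, which is part of the stated aim.

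**The case against.** **The design may be sound and the wording loose.** Two sections describe randomisation to four groups, and the flow diagram and timeline, which are not shown here, might clarify the path. However, decliners are admitted in two separate sections, one of which describes how they are approached. A diagram could not cancel those sentences.

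**Confounding is to be handled in the analysis.** Covariates and Confounders lists preintervention sleep scores, medication and comorbidities, and Limitations relies on a good baseline study. This would help with measured differences, and the illustration above is unadjusted. But the list contains no measure of treatment preference or motivation, and Statistics adjusts only for covariates found significant. Unmeasured selection would remain. How much of a measured imbalance could be adjusted away with 12 to 15 patients per arm was not computed.

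**Readings that go too far.**

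- A reader might infer that the control arm consists entirely of refusers. The text equally allows a mixture, and the higher rates in the table hold only if all controls are decliners.
- A reader might infer that decliners are selected directly on the primary outcomes through anxiety or motivation. Anxiety (STAI) is not among the listed primary outcomes, perceived stress is secondary, and motivation is not an outcome. Only sleep complaint overlaps directly, and for the hormone measures the link is less direct.
- A reader might cite the Randomization section as explicitly covering the control arm. It does not.

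**Conclusion.** The plan is wrong as written. It gives two incompatible sources for the control arm, and if the decliner provisions are followed, every comparison with the pooled control becomes at least partly non-randomised. The claim of superiority over no intervention depends on exactly that comparison.

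The contradiction and the loss of randomisation follow from the text alone. The size does not. Under the assumed differences of 0.3 to 0.5 SD, the per-contrast false-positive rate rises from 5% to between about 6% (half decliners, 0.3 SD, n = 12) and about 26% (all decliners, 0.5 SD, n = 15). Bias in the opposite direction to a real benefit could conceal it instead.

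It would be too strong to say that the whole trial is non-randomised, because contrasts among the three active arms stand.

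**What to change.** - State once, and consistently in Overview, Study Population, Eligibility and Randomization, that consenting eligible patients are randomised 1:1:1:1, with no intervention as one of the four allocations.
- Delete the Overview sentence that brings patients unwilling to be randomised into the control group, and the Eligibility option offering that group to people who decline the trial.
- If decliners are to be followed, define them as a separate observational cohort. Exclude them from all primary and secondary comparisons and from the 12 (15 with dropout allowance) per group.

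The planned number per group does not change. The cost is protocol wording, which is cheap now because the trial has neither started nor been registered. Recruitment may also be slower, since decliners no longer count as controls. By how much cannot be estimated from the documents, but it should not be dismissed: Limitations already names recruitment as a difficulty, and Overview relies on one local foundation and a preintervention period of 1.5 years.

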**Figure 1 figure1:**
[figure not shown]
Flow diagram illustrating the study protocol. At the allocation to interventions, the number of patients who receive the intervention will be registered, as well as those who do not receive it (together with the reason it was not applied) and those who get lost in the follow-up or discontinue the intervention. In addition, unbearable side effects and SUSARs would be appropriately notified and registered. e: patients excluded; r: randomized patients; RP: retinitis pigmentosa; SUSAR: suspected unexpected serious adverse reaction; SWL: short-wavelength light; VA: visual acuity.

**Table 1 table1:** Protocols of the intervention.

Group	Preintervention period (2 weeks)	Intervention period (30 days)
SWL^a^: optical SWL filters	Sleep diary	Sleep diary, goggles
OM^b^	Sleep diary	Sleep diary, OM
SWL+OM: optical SWL filters and OM	Sleep diary	Sleep diary, goggles, OM
Control: no intervention	Sleep diary	None

^a^SWL: short-wavelength light.

^b^OM: oral melatonin.

**Figure 2 figure2:**
[figure not shown]
RCT timeline. RCT: randomized controlled trial.

### Study Population

The study population will comprise patients aged 18-65 years with a history of moderate or severe RP with a grading severity scale score of >1 point according to Iftikhar et al’s [83] scoring criteria. Eligible patients who provide written informed consent will be randomized to 1 of the 4 study groups. Outcomes will be assessed at multiple time points: at baseline in the preintervention period; then at 1, 2, 3, and 4 weeks of the intervention period; and then at 6 months postintervention.

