**Methods:**

We have developed a low-cost therapy protocol for patients with RP with sleep disorders and negative psychological stress. Patients will be randomized to receive a combined intervention with SWL-blocking filters and OM, SWL-blocking filters alone, or OM alone. There will also be a nonintervention arm as a control group. This study will be conducted across 2 retinal units in patients with RP with sleep disorders and high perceived stress and anxiety score reports. Patients will be assessed in the preintervention period, weekly during the 4 weeks of intervention, and then at 6 months postintervention. The primary outcomes are the differences in changes from baseline to postintervention in hormone release (α-amylase, cortisol, and melatonin) and sleep quality, as measured with the visual analog scale. Secondary outcome measures include clinical macular changes, as measured with optical coherence tomography and optical coherence tomography angiography; retinal function, as measured using the visual field and best-corrected visual acuity; sleep data collected from personal wearables; and several patient-reported variables, such as self-recorded sleep diaries, quality of life, perceived stress, and functional status.

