The aim of this study is to assess the efficacy of OM combined with SWL-blocking filters in patients with RP who have sleep disorders and stress compared to any intervention alone or no intervention. We hypothesized that both interventions would improve their sleep quality, reduce their perceived stress levels, and shift their circadian rhythm to morningness.

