#### Recruitment

##### Screening Visit

Patients will undergo an initial screening visit that includes a semistructured interview, a series of questionnaires, a complete ophthalmic examination, and laboratory assessment. Eligible patients will be provided with a verbal description of the trial and presented with a comprehensible informed consent form.

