##### Laboratory Assessment

All patients will undergo a salivary and hair draw to confirm eligibility. Sample collection will be carried out between 9:00 A.M. and noon to minimize potential errors associated with diurnal variations in neuroendocrine parameters. Samples will be collected in the same room, and temperature and humidity will be recorded. After collection, samples will be frozen at –20 °C until analysis. When analyzing results, in female subjects, menstrual cycle phases will be considered.

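### The aim names RP patients with sleep disorders and stress, but no entry criterion requires either, so patients with normal sleep and low stress can be randomized

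*Protocol article*

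**What the plan says.** The abstract's Methods place the trial in "patients with RP with sleep disorders and high perceived stress and anxiety score reports". The aim, at the end of Background and Rationale, concerns "patients with RP who have sleep disorders and stress compared to any intervention alone or no intervention".

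The operative definition is different. Under Study Population: "The study population will comprise patients aged 18-65 years with a history of moderate or severe RP with a grading severity scale score" above 1 point. Under Eligibility: "Eligibility will be determined based on the inclusion and exclusion criteria listed in Table 2". The inclusion column of Table 2 has four items: age with ReCYL membership, RP severity, "Visual function enough to tolerate and see through the optic filters during daily activities", and written consent. None concerns sleep, stress or anxiety. Among the exclusions is "Psychiatric disorders or under any psychotropic medication".

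The main text makes change in ESS and PSQI primary, together with the salivary and hair biomarkers. The section on the two scales gives the PSQI a range of 0 to 21 with lower scores better, and sets the minimum important improvement on both scales between −2 and −3.

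**The concern.** The article names one population and selects another. Followed as printed, the criteria admit a patient with moderate or severe RP who sleeps well and reports little stress. Two things are at stake.

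- **Interpretation.** The conclusions speak of lessening the effect of sleep and psychological disorders on quality of life. A sample not selected for those problems does not directly support them.
- **Sensitivity of the questionnaire outcomes.** Good sleepers sit near the bottom of the PSQI and ESS. They have little room to fall, so they can pull the mean change in a treated arm towards zero. With 12 to 15 patients per arm there is little margin to absorb that.

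**Working it through.** **1. The descriptions side by side**

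| Place | Population described |
|---|---|
| Abstract, Methods | RP with sleep disorders and high stress and anxiety scores |
| Background and Rationale, aim | RP with sleep disorders and stress |
| Abstract, Objective | RP; sleep problems attributed to many patients, not all |
| Need for a Trial; Conclusion | Moderate or severe RP |
| Study Population; Table 2 | Age, RP severity, ReCYL, usable vision, consent |

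**2. Does another section supply the criterion?**

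- Screening Visit: "Patients will undergo an initial screening visit that includes a semistructured interview, a series of questionnaires, a complete ophthalmic examination, and laboratory assessment". No score is tied to entry.
- The STAI, ESS and PSQI sections give important differences for judging change, not entry cut-offs.
- Laboratory Assessment: "All patients will undergo a salivary and hair draw to confirm eligibility". No biomarker limit is stated.
- Eligibility mentions qualifying procedures without defining them.
- Table 3 ticks the inclusion criteria at V−1 and the three questionnaires at V0 and V4 only. The text on baseline assessments puts baseline measures at the screening visit. On either reading no score decides entry.

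**3. Headroom on the PSQI**

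The largest possible improvement equals the baseline score, because the scale stops at 0.

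- Baseline 0 or 1: the most it can fall is 0 or 1, so −2 is out of reach.
- Baseline 2: −2 is reachable, −3 is not.
- Baseline 3 or more: both are reachable.

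**4. The plan's own sample size**

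Inputs from Sample Size Calculation: d = 1.2, 12 per group, α = 5% (two-sided assumed), stated power 80.02%.

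For a two-sample t test the noncentrality is d × √(n/2) = 1.2 × √6 = 2.94 on 22 degrees of freedom. Power is 80.2%. Solving for n gives 11.94, hence 12. With 20% dropout, 12 / (1 − 0.20) = 15 per group, 60 in all. The stated design reproduces.

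**5. Illustration of dilution**

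Let q be the share of enrolled patients who cannot respond. This is an assumption; the documents give no figure. If the others respond with d = 1.2 and the SD is unchanged, the overall effect is 1.2 × (1 − q).

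| q | Overall d | Power, 12 per group | Power, 15 per group | n per group for 80% |
|---|---|---|---|---|
| 0% | 1.20 | 80% | 89% | 12 |
| 20% | 0.96 | 61% | 72% | 19 |
| 30% | 0.84 | 50% | 60% | 24 |
| 50% | 0.60 | 29% | 35% | 45 |

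Mixing responders and non-responders also widens the spread in the treated arm. Dividing d by √(1 + q(1 − q) × 1.2² / 2) gives 57%, 45% and 25% at 12 per group for q = 20%, 30% and 50%. A floor would act the other way by compressing the SD.

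**The case against.** The strongest reply is that the article does not restrict its population consistently. The abstract's Objective, the Need for a Trial section and the Conclusion all describe RP patients in terms compatible with Table 2. That stands. It means the narrower wording may be the error, so correcting the wording is as well supported as adding thresholds.

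A reader might infer that patients without room to improve will be enrolled. The documents do not support that, because they give no prevalence of poor sleep or stress among ReCYL members. They show only that such patients can enter.

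A reader might also infer from Table 3 that the questionnaires come too late to be used for selection. The text puts questionnaires at screening, and the randomization code is withheld until baseline measurements are complete. Scores would therefore exist before allocation. The defect is the missing criterion; the Table 3 placement is a secondary inconsistency.

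The power figures are open to fair challenge:

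- The non-responder shares are assumed.
- The article does not say which endpoint d = 1.2 refers to. If it came from unselected patients, the dilution is already in it.
- The floor argument applies to the questionnaires, not directly to amylase, cortisol or melatonin.
- The same section also says that an effect of 0.6 was chosen. That conflict is a separate matter, and the table uses 1.2 only because it reproduces 12 per group.

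These points reduce the table to an illustration. They do not touch the contradiction, which needs no assumed number.

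**Conclusion.** The point holds as a contradiction between the named and the operative population. Two places restrict the trial to patients with disturbed sleep and stress, the section and table that decide entry do not, and nothing else in the article fills the gap. This is not an effect of condensing a longer protocol, since the article prints the eligibility table and says that it governs.

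The consequence that follows from the documents alone is limited. Patients with normal sleep and low stress can be randomized. Those with a baseline PSQI of 0 or 1 cannot reach any part of the −2 to −3 range, and those at 2 cannot reach −3. Results from such a sample would not describe the population in the aim.

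The fall in power from 80% to between 61% and 29% is conditional. It rests on assumed shares of 20% to 50%, on no effect at all in those patients, on d = 1.2 in the rest, and on that d applying to a questionnaire outcome. It should not be read as the trial's expected power.

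The exclusion of psychiatric disorders and psychotropic medication may remove some of the anxious patients the abstract targets. The documents do not show how many.

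**What to change.** Reconcile the passages before launch, in one of two ways.

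**(a) Select the named population.** Add to Table 2 entry thresholds on PSQI and/or ESS and on STAI, fixed by the steering committee before the first patient. They should define disturbed sleep and raised stress or anxiety. A minimum chosen only so that −3 is attainable would be a PSQI of 3, which gives headroom but does not identify a sleep disorder. Mark these questionnaires at V−1 in Table 3, in line with the screening and baseline text. State how the anxiety criterion fits with the psychiatric and psychotropic exclusion. The cost is protocol wording, at most one extra administration of questionnaires already planned, and a smaller eligible pool in a trial whose Limitations section already expects recruitment difficulty.

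**(b) Keep all comers.** Remove the sleep and stress restriction from the abstract's Methods and the aim, and word the conclusions for unselected moderate or severe RP. The sample size should then rest on an effect expected in that wider group. The change costs wording only, but the trial would no longer speak directly to patients with sleep disorders.

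Either is cheap now, because the article reports that the trial has neither started nor been registered.
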